#### 4.3.2. M-PAC Constructs for Physical Activity

Constructs of affective attitude, instrumental attitude, and perceived behavioral control are assessed using the constructs of the theory of planned behavior [85]. Behavioral regulation is measured via items adapted from Sniehotta et al. [86] and Umstattd’s scale measuring physical activity self-regulation strategies in older adults [86]. Exercise identity (whether participants identify as being an exerciser) is measured via a modified exercise identity scale from Anderson and colleagues [1994, 1995, 1998]. Measures from these instruments have demonstrated excellent predictive validity and internal consistency in adult [61,87,88,89] samples, such as Self-Report Habit Index items from the measure developed by Verplanken and Orbell [90] and adapted to physical activity by Chatzisarantis and Hagger [91]. Finally, Anderson and Cychosz’s Exercise Identity Scale is used to measure participants’ identification as someone who participates in physical activity [92].

#### 4.3.3. Quality of Life

Psychosocial outcomes are primarily assessed using the short-form 12 (SF-12) health survey which measures health-related quality of life on a range of functional domains including vitality, social functioning, and overall well-being [93]. The SF-12 has been validated for adult populations with established evidence for reliability [94].

### 4.4. Post-Intervention Qualitative Interview

The process evaluation procedures involve a brief quantitative questionnaire to assess the use of the intervention material and overall satisfaction of the study. Intervention condition participants also have the option of participating in an in-person exit interview to explore the acceptability of the intervention and associated study procedures. In order to examine the possible mechanisms of change as well as suggestions for future intervention development and study procedures, participants’ views concerning the impact of the intervention are explored. The interview guide is semi-structured and includes 10 open-ended questions; it was informed by previous research examining the acceptability of online interventions and qualitative process evaluations that have proved useful in our prior evaluations [69]. To minimize bias, these interviews are facilitated by a research coordinator or assistant unaffiliated to the study. Audio recordings of interviews are to be transcribed verbatim and analyzed using a content and thematic analysis. All data are to be stored securely, and raw data are only to be accessible to the study chief investigator [name] and researcher [name].

### 4.5. Qualitative Analysis

Data from the exit interviews will be analyzed based on a thematic approach [95]. Research team members will read through the transcripts for familiarization, after which items of analytic interest will be identified, and an initial coding framework developed. Through repeated readings of the transcripts, a framework of patterns and concepts will be linked iteratively across interviews and refined though research memos and team meetings to discuss the emergent themes. For each theme, data extracts will be compiled on the basis of being representative and elaborating upon the research questions [96,97]. The reliability and validity of the analysis will be enhanced through an iterative data analysis, the use of a multi-method design, and the ongoing discussion of findings within the research team for scrutiny and feedback [97]. We will follow recommendations from previous literature [69,98] to reduce bias by analyzing the process data before the trial outcomes are known. The qualitative analysis procedure will be research question-oriented and anchored to the quantitative analysis [69,98].

## 5. Data Analyses

Data analyses will primarily be descriptive and address the outcomes relating to the feasibility of the intervention and study procedures. Progression criteria will be used to determine whether revisions should be considered before proceeding to a controlled trial.

### Quantitative Analyses

An adapted CONSORT diagram (Figure 1) for pilot and feasibility studies has been used to illustrate participant flow. Numbers of participants recruited by advertisements, flyers, in-person, etc., expressing initial interest, consented, assessed for eligibility, eligible, and included, are reported. Percentages of participants meeting the eligibility criteria of the participants assessed for eligibility, and participants eligible of the total number enrolled will be calculated. Reasons for ineligibility, ambiguities regarding eligibility criteria, and reasons for non-participation will be reported at each stage.

Follow-up rates will be calculated with 95% Confidence Intervals. Descriptive statistics for each outcome measurement at the eligibility interview, baseline and at the 10-week follow-up will be reported. Attrition proportions (for both intervention and study dropouts) will be reported.

Means, SDs, and frequencies for each portal activity relating to intervention adherence and use, including log-ins, opened modules and items, completed action plans, and use of optional support will be reported. Potential ambiguities regarding eligibility and other procedures will be tabulated into an Excel form and reported statistically. Types and numbers of measures undertaken and numbers of unforeseen safety issues, if any, will be reported.

## 6. Ethics

The study has been approved by the University of Victoria’s Human Research Ethical Review Board (HREB) in Victoria BC. Participant confidentiality is guaranteed. Informed consent is collected to ensure participants are aware of the conditions of the study participation. Participants are reminded of their rights to withdraw from the study without giving any reason. Participants are provided contact information within the study consent form for both the principal investigator, the study coordinator, and the independent UVIC HREB group should they have any cause for concern regarding the conduct of the trial. All participants are assigned a study code to de-identify the data and personal information about participants stored separately from the de-identified data. Data collected via the portal are to be stored on secure servers at University of Victoria, BC, Canada. All other data are stored in a locked filing cabinet, accessible only to the study personnel.

### Data Management and Confidentiality

Confidentiality procedures are outlined in the consent form and explicated during informed consent procedures conducted by the research coordinator at the baseline assessment. Each participant is provided with an identification number. Hard copies of any documentation are kept in a locked and secure environment (locked laboratory and cabinets) at the University of Victoria. Any data or personal information stored on computers are kept on a secure server. Questionnaire data are stored on SurveyMonkey servers in Canada.

## 7. Dissemination

The findings of the study and the subsequent proposal for the full-scale RCT will be presented to potential collaborators including local health authorities, governmental organizations, community organizations, and others through presentations at educational events. We will also disseminate the findings of the feasibility study and the proposed RCT to local, national, and international conferences as presentations and in scientific journals as published manuscripts. Participants who express interest in the study results will be made aware of any relevant publications. Public access to the participant level dataset will not be granted. There are no current plans to grant public access to the full protocol. All authors who have contributed to the protocol design are eligible for authorship on subsequent publications.

## 8. Results

At the time of submission (29 March 2020), we have obtained ethical approval, registered the trial, and recruited 31 participants. Recruitment is expected to be complete by the end of 2020. From the 31 participants recruited, 31 have completed the baseline measures, 19 have completed the 10-week measures, 19 have completed the study, and 2 have dropped out. See Figure 1 for the study procedures and participant flow chart.

## 9. Discussion

This protocol describes the implementation of a randomized controlled feasibility trial employing an online platform to increase physical activity behavior within recently empty nest or retired participants, based on the assumptions of the M-PAC framework as a conceptual model. Research findings will be important to public health as they may help to determine if providing low-cost, scalable, and evidence-based planning strategies for family physical activity can aid in producing higher adherence to physical activity.

## 10. Conclusions

The results of this feasibility study will inform the planning of a definitive RCT, by assessing the rates of recruitment, retention, adverse events, and data collection. The qualitative analysis will be used to further refine the empty nest/retirement-tailored online platform and the study protocol for the proposed trial. This randomized feasibility trial will build on PA promotion, habit discontinuity, and life-course research, evaluating whether an online PA intervention at the empty nest or retirement stage of life is an effective time point to promote PA. This study will also test the novel multi-process action control framework approach to PA-related behavioral change, exploring how reflexive processes of habit and identity may bridge adoption and maintenance in behavioral adherence.

## Figures and Tables

**Figure 1 ijerph-17-03544-f001:**
[figure not shown]
CONSORT 2010 Flow Diagram.

**Table 1 ijerph-17-03544-t001:** Overview of online platform lesson content linked to the theoretical/behavioral concepts used in this study.

	Title and Description	Corresponding Multi-Process Action Control Model Concept
Lesson 1	“Benefits of Physical Activity on Chronic Disease”	Initiating reflective processes (instrumental attitude, outcome expectations)
Lesson 2	“Mental benefits of Physical Activities”	Initiating reflective processes (instrumental attitude, outcome expectations)
Lesson 3	“Increasing Self Confidence for Physical Activities”	Initiating reflective processes (perceived capability)
Lesson 4	“Learning about your Emotion”	Ongoing reflective processes (affective attitude)
Lesson 5	“Building Social Support”	Ongoing reflective processes (affective attitude)
Lesson 6	“Building Physical Activity Opportunity”	Ongoing reflective processes (affective attitude)
Lesson 7	“Goal Setting and Planning”	Regulation processes Regulation
Lesson 8	“Self-Monitoring”	Regulation processes Regulation
Lesson 9	“Habit”	Regulation processes, reflexive processes (habit)
Lesson 10	“Identity”	Regulation processes, reflexive processes (identity)

**Table 2 ijerph-17-03544-t002:** Overview of feasibility outcomes and progression criteria, adapted from Woodford et al. (2018) [76].

Outcome	Evaluation Measures	Assessment Criteria for Progression
Recruitment and eligibility	Recruitment strategy	No criteria set
	Percentage assessed for eligibility; fulfilling inclusion criteria, and consented to participate (of total number screened)	1 day per week or 30 min MVPA change which equates to an approximate effect size of d = 0.35. This equates to roughly 65 per group (130 for a two-group trial). If we recruit for 2 years in the large trial (assuming a six-month time period for each person in the intervention) we need to be recruiting at least 6 per month. If we decide on a three armed trial, we will need to recruit at least 8 per month [77].
	Ambiguities regarding eligibility criteria	No criteria set
	Reasons for ineligibility	No criteria set
	Reasons for non-participation	No criteria set
Attrition	Rates of study dropout Rates of intervention dropout	70 > % 70 > % [78]
Resources needed to complete the study and the intervention	Length of time and cost required for: Study staff and resources required to administer the study Technical support required for online platform	No criteria set
Intervention Condition Participant Adherence	Number of: Opened modules, completed action plans Completed telephone check ins	70% > completing the introductory chapter, 10 modules and 2- and 5-week check in calls Full adherence to the intervention will be defined as: (1) completion of baseline meeting and questionnaire; (2) completion of all modules (3) completion of final questionnaire.
Participants’ use of the intervention/usage attrition	Number of: Log-ins Modules opened completed action plans/activities Time spent on each module	No criteria set
Participants’ acceptability and satisfaction with intervention	Reasons for withdrawal from study and intervention, reasons for not engaging with the online platform material.	No criteria set
	Participant feedback on the intervention material (including positive and negative) and of completing study procedures	70% > of participants using the intervention reporting that it is helpful 30% < participant reporting substantial negative consequences related to participation in the study and/or intervention [69].

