## Abstract

Despite the extensive evidence on the benefits of physical activity (PA) in older adults, including reduced risk of disease, mortality, falls, and cognitive and functional decline, most do not attain sufficient PA levels. Theoretical work suggests that behavioral change interventions are most effective during life transitions, and as such, a theory-based, online intervention tailored for recently retired and empty nest individuals could lend support for increasing levels of PA. The aim of this study is to examine the feasibility of the intervention and study procedures for a future controlled trial. This study has a randomized controlled trial design with an embedded qualitative and quantitative process evaluation. Participants are randomized at 1:1 between the intervention and waitlist controls. Potential participants are within six months of their final child leaving the familial home or within six months of retiring (self-defined), currently not meeting the Canadian PA guidelines, have no serious contraindications to exercise, and are residing in Victoria, British Columbia, Canada. Participants are recruited by online and print flyers as well as in-person at community events. The study aims to recruit 40 empty nest and 40 retired participants; half of each group received the intervention during the study period. The internet-delivered intervention is delivered over a 10-week period, comprising 10 modules addressing behavior change techniques associated with PA. Primary outcomes relate to recruitment, attrition, data collection, intervention delivery, and acceptability. Secondary behavioral outcomes are measured at baseline and post-treatment (10 weeks). Intervention-selected participants are invited to an optional qualitative exit interview. The results of this feasibility study will inform the planning of a randomized effectiveness trial, that will examine the behavior change, health-related fitness, and well-being outcomes by exploring how reflexive processes of habit and identity may bridge adoption and maintenance in behavioral adherence.

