### 3.2. Eligibility Criteria

The eligible population includes recently retired and empty nest individuals, who are in addition not currently meeting PA guidelines (attaining less than 150 min of MVPA per week). We used the previous 6 months to delineate a split of “recent” or “not recently” retired, or had their last child leave the family home; however, we acknowledge that this split is relatively arbitrary and 12 months may encourage a larger reach of participants.

In other work exploring the habit discontinuity thesis, Verplanken et al. (2008) suggested that a period of 12 months may be suitable to evaluate the effects on travel mode use after moving home [39]. Later work broadly supports this concept, however, the strongest differences in the predicted probability were observed in the very early months after moving home, and soon decreased over time, suggesting a declining influence of contextual changes [71].

Exclusion criteria for our study were as follows: have not retired (self-defined) within 6 months or last child has not moved out of the familial home within 6 months. Participants are excluded if they are unable to speak and read English, and do not have access to the internet, a smart phone, or computer that can support the eHealth application we are using for the intervention. In addition, as assessed by the Get Active Questionnaire (GAQ) 2017, developed by the Canadian Society for Exercise Physiology (CSEP), a documented or patient-reported medical condition that would preclude participation, including within 6 months of having a diagnosis of/treatment for heart disease or stroke, or pain/discomfort/pressure in the chest during activities of daily living or during physical activity, a diagnosis of/treatment for high blood pressure, or a resting BP of 160/90 mmHg or higher, dizziness or lightheadedness during physical activity, shortness of breath at rest, loss of consciousness or fainting for any reason, concussion, pain or swelling in any part of the body (such as from an injury, acute flare-up of arthritis), or any other clinical condition that the person’s GP or clinician considers would make them unsuitable for participation in a physical activity program (such as diabetes, cancer, osteoporosis, asthma, spinal cord injury) [72]. Following recommendations of sample sizes of 50–60 being appropriate to assess the feasibility outcomes and estimate the sample size for a definite trial, we aim to recruit 80 participants [73].

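### The 65 per group behind the recruitment progression thresholds does not follow from d = 0.35 in an unadjusted two-group trial, which needs about 130 per group, so 6 and 8 per month are probably too lenient

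*Protocol article*

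**What the plan says.** The recruitment and eligibility block of Table 2 has one numerical progression criterion; its other rows set none. The criterion is built in three steps.

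- Target effect: "1 day per week or 30 min MVPA change which equates to an approximate effect size of d = 0.35".
- Sample size: "an approximate effect size of d = 0.35. This equates to roughly 65 per group (130 for a two-group trial"). The total of 130 implies two equal groups, in line with the feasibility study itself: "Participants are randomized at 1:1 between the intervention and waitlist controls" (Abstract).
- Monthly rate: with two years of recruitment, and six months in the intervention for each person, "we need to be recruiting at least 6 per month". For a further arm, "If we decide on a three armed trial, we will need to recruit at least 8 per month".

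For this figure the article gives no alpha, sidedness, power, analysis model, baseline correlation, number of follow-up assessments or dropout allowance.

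**The concern.** The cell presents the sample size as following from the effect size, so the step can be checked on the page. For a comparison of two independent means, 65 per group is about half the usual requirement at d = 0.35. Two coincidences suggest a slip: the stated total of 130 equals the usual number per group, and a one-sample or paired formula gives about 65.

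What is at stake is the feasibility decision. Sections 4.1 and 5 say that the progression criteria guide whether to go on to a full-scale trial and whether to revise first. If the sample size is too small by a factor of two, so are the monthly rates, and a study that recruits too slowly for an adequately powered trial could still pass.

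The threshold is close enough to matter. Section 8 reports 31 recruits by 29 March 2020. Ethics approval was on 18 September 2019 (Section 3), about 6.3 months earlier. The start of recruitment is not stated. If it did not precede approval, the rate is at least 31/6.3 = 4.9 per month, and a five-month period would give 31/5 = 6.2. That range straddles 6 and is roughly half of 11.

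**Working it through.** **Inputs.** From Table 2: d = 0.35, 65 per group, 130 in total, two years, 6 and 8 per month. Assumed because not stated: two-sided alpha 0.05, 80% power, no covariate adjustment, no dropout. Alternatives are shown.

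**1. The plan's monthly rates, taking 65 per group as given.**
- Two arms: 130/24 = 5.4, stated as 6.
- Three arms: 3 × 65 = 195; 195/24 = 8.1, stated as 8.

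The rates therefore come from 65 per group spread over the full 24 months.

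**2. The sample size for two independent means.**
n per group = 2(z₁₋α/₂ + z₁₋β)²/d² = 2(1.960 + 0.842)²/0.35² = 15.70/0.1225 = 128.1, so 129. The t-test calculation gives 129.1, so 130 per group and 260 in total.

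| Alpha | Power | n per group (normal approximation) |
|---|---|---|
| two-sided 5% | 70% | 101 |
| two-sided 5% | 80% | 129 |
| two-sided 5% | 90% | 172 |
| one-sided 5% | 70% | 77 |
| one-sided 5% | 80% | 101 |
| one-sided 5% | 90% | 140 |
| one-sided 10% | 70% | 54 |
| one-sided 10% | 80% | 74 |
| one-sided 10% | 90% | 108 |

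The t-test adds about one per group (102 at one-sided 5% and 80% power; 173 at two-sided 5% and 90% power). No row gives 65. It falls between the 70% and 80% rows at one-sided 10%, which is not a usual setting for a definitive trial.

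**3. What 65 per group delivers.**
- Power: d√(n/2) = 0.35 × √32.5 = 1.995; 1.995 − 1.960 = 0.035, so about 51% two-sided (51.4% normal, 50.8% t-test). One-sided 5% gives about 63–64%.
- Detectable effect at 80% power: 2.802 × √(2/65) = 0.491 (0.495 by t-test). The SD implied by Table 2 is 30/0.35 = 86 min, so this is about 0.495 × 86 = 42 min rather than 30.

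**4. Ways to arrive at 65.**
- One-sample or paired formula: (2.802/0.35)² = 64.07, rounded up to 65 (about 66 by t-test). This does not suit a between-group comparison.
- ANCOVA with one follow-up: 128.1 × (1 − r²) gives 117 at r = 0.3, 97 at r = 0.5 and 66 at r = 0.7. It equals 65 at r = 0.70.
- Change scores, with d scaled by the cross-sectional SD: 128.1 × 2(1 − r) gives 65 at r = 0.75. If d is already scaled by the SD of change, the requirement returns to 129–130.
- ANCOVA on the mean of two follow-ups, all correlations equal to r: the factor is (1 + r)/2 − r². At r = 0.5 it is 0.75 − 0.25 = 0.50, and 129.1 × 0.50 = 64.6, so 65.

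**5. Monthly rates at 130 per group, before dropout.**

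| Enrolment | Two arms (260) | Three arms (390) |
|---|---|---|
| 24 months | 10.8, so 11 | 16.25, so 17 |
| 18 months | 14.4, so 15 | 21.7, so 22 |

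The 18-month row applies if the last entrant must finish six months of intervention within the two years. On that reading even 130 in total needs 130/18 = 7.2 per month, above the stated 6. The three-arm column assumes 130 in each arm and makes no allowance for multiple comparisons.

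**The case against.** The strongest reply is that the inputs are unstated and the number is not proven wrong. The article is condensed, the figure is an approximate planning number for a different, future trial, and the source cited at the end of the cell is not at hand. An adjusted analysis could produce 65, and not only with a high correlation: two follow-ups averaged at r = 0.5 are enough. The single 10-week follow-up belongs to the feasibility study, and the number of assessments in the later trial is not given. This stands, and it rules out saying flatly that the figure is half what it should be. It does not rescue the text, because the cell gives 65 as a consequence of d = 0.35 alone. Nor should r = 0.70 be presumed for self-reported activity minutes (Section 4.3.1) in people selected for being below 150 min per week (Section 3.2).

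A reader might also infer that a positive decision would launch a definitive trial with about a 50% chance of detecting its own target. The documents do not support that. Section 3.2 justifies the feasibility sample by a recommendation on sizes "appropriate to assess the feasibility outcomes and estimate the sample size for a definite trial", and Sections 4.1, 5 and 10 describe the results as guidance and as informing planning. The sample size may be re-estimated first. Section 3.2 is therefore not a second instance of the problem; it limits the consequence.

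**Conclusion.** The point holds in a limited form. The 65 per group in Table 2 is not reproduced by any conventional unadjusted two-group calculation at d = 0.35. At two-sided 5% and 80% power the requirement is about 130 per group, twice the printed figure. The factor depends on those assumptions: it is about 1.6 at one-sided 5% (102/65) and about 2.7 at 90% power two-sided (173/65). The figure could be correct only under an adjusted design that the article does not describe.

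The consequence is confined to the recruitment progression check. Thresholds of 6 and 8 per month are probably about half what an unadjusted trial would need, so the check is too lenient. The conduct, size and descriptive analysis of the feasibility study are not affected.

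**What to change.** Amend the recruitment cell of Table 2 in one of three ways:

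1. Replace the sample size with about 130 per group (260 for two groups; 80% power, two-sided 5%) and re-derive the rates: about 11 per month for two arms and 17 for three over 24 months of enrolment, or about 15 and 22 over 18 months. Say which enrolment window applies, and that the rates are before attrition and before any multiplicity allowance for three arms.
2. Keep 65 per group and restate the effect detectable with 80% power as about d = 0.50, roughly 42 min at the implied SD.
3. Keep 65 per group and d = 0.35, and state the alpha, power, analysis model, number of follow-ups and baseline correlation that justify them.

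The cost is wording in one cell. Under the first option the recruitment target becomes harder to meet; under the second, the future trial is no longer sized for a 30-min change; the third commits the future trial to a correlation that can be challenged. None changes how the feasibility study is run.

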## 4. Data Collection

### 4.1. Primary Outcome Measures

The key feasibility outcomes examined via the proposed protocol concern the evaluation of study methods and procedures, including estimates of likely recruitment and retention rates, feasibility and acceptability of the intervention, and tests of the study procedures [75]. Following CONSORT, between group improvements regarding behavioral outcomes and efficacy are not examined at this stage. An embedded qualitative process evaluation will be used to examine:The acceptability of the intervention;Participants’ self-reported PA support needs;Potential mechanisms of change;The impact of the intervention.

Feasibility outcomes are shown in Table 2, adapted from Woodford et al. [76]. Progression criteria have been set a priori to facilitate a feasibility data analysis and provide guidance about whether to proceed to a future full-scale trial.

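### Table 2 puts the 70% attrition criterion on dropout, and no single reading of the column's inequality signs makes the progression criteria agree

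*Protocol article*

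**What the plan says.** Table 2 of the protocol article has a column headed "Assessment Criteria for Progression". Four kinds of row in it carry a percentage threshold:

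- **Attrition.** The measures are "Rates of study dropout Rates of intervention dropout". The criterion, given once for each, is `70 > %`, with a citation.
- **Adherence.** "70% > completing the introductory chapter, 10 modules and 2- and 5-week check in calls".
- **Helpfulness.** "70% > of participants using the intervention reporting that it is helpful".
- **Negative consequences.** "30% < participant reporting substantial negative consequences related to participation in the study and/or intervention".

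Nothing in the article explains the signs or says that the attrition figure refers to participants kept rather than lost. Section 4.1 gives the purpose of the column: "Progression criteria have been set a priori to facilitate a feasibility data analysis and provide guidance about whether to proceed". Section 5 says the criteria will be used to decide whether revisions should be considered before a controlled trial. Retention is part of the first research question in Section 2.

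**The concern.** A threshold of 70 attached to a dropout rate is hard to read sensibly in either direction. As a floor it asks for most of the sample to be lost. As a ceiling it lets most of the sample be lost. The neighbouring rows do not settle the matter, because whichever convention makes them sensible makes the attrition rows wrong.

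Most rows of Table 2 set no criterion, so attrition is one of the few numeric thresholds available to guide the decision on a full-scale trial. If its meaning is chosen after the retention data are known, it is no longer an a priori criterion.

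**Working it through.** **Inputs.** The Table 2 thresholds are as set out above. The planned sample is 80 (Section 3.2), with half of each group of 40 receiving the intervention (Abstract), so about 40 per arm. The interim flow is 31 recruited, 19 with 10-week measures completed and 2 dropouts (Section 8). The 70% is a chosen threshold, not a computed figure, so there is nothing to reproduce. The check is on direction and consequence.

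**Step 1: direction of each row.** The desirable direction is low dropout, high adherence, high helpfulness and few negative consequences. Each sign convention is read with the column as criteria for going ahead.

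| Row | Convention A: `70% >` is more than 70%, `30% <` is less than 30% | Convention B: literal, 70 > x and 30 < x |
|---|---|---|
| Study and intervention dropout | above 70%: reversed | below 70%: right direction |
| Adherence | above 70%: right | below 70%: reversed |
| Helpful | above 70%: right | below 70%: reversed |
| Negative consequences | below 30%: right | above 30%: reversed |

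If the column is read as criteria for stopping, every entry flips. In all four combinations the attrition rows conflict with the other three.

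**Step 2: the counts at 80 participants.**

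- Convention A: dropout > 0.70 × 80 = 56, so at least 57 dropouts (57/80 = 71.25%).
- Convention B: dropout < 56, so up to 55 dropouts (55/80 = 68.75%), leaving 80 − 55 = 25.
- Retention above 70%: retained > 56, so at least 57 retained and at most 80 − 57 = 23 dropouts. Dropout below 30% (fewer than 0.30 × 80 = 24) gives the same limit.

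**Step 3: chance of meeting each version**, assuming independent dropouts with a common true rate, n = 80, binomial.

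| True dropout | Dropout > 70% | Dropout < 70% | Retention > 70% |
|---|---|---|---|
| 10% | about 0 | about 1 | about 1 |
| 30% | about 0 | about 1 | 0.458 |
| 50% | 0.0001 | 0.9998 | 0.0001 |
| 65% | 0.145 | 0.793 | about 0 |

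The two plausible versions, dropout < 70% and retention > 70%, agree when dropout is low. At a true dropout of 50% they give almost opposite answers.

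**Step 4: reading only the attrition row literally.** The sign is placed differently there (`70 > %` against `70% >`), so a mixed reading is possible.

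- *Intervention dropout.* With 40 in the intervention arm, adherence above 70% needs more than 28, so at least 29 who complete everything and at most 40 − 29 = 11 who could have left the intervention. A 70% ceiling on intervention dropout then never operates.
- *Study dropout.* Suppose those 29 also return the final questionnaire. Losing the other 11 and the whole waitlist arm gives (11 + 40)/80 = 51/80 = 63.75%, which still satisfies dropout below 70%.

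**Step 5: interim data.** Among participants with a known outcome, retention is 19/21 = 90.5% (exact 95% CI 69.6% to 98.8%) and dropout is 2/21 = 9.5%. Of all recruited, dropout so far is 2/31 = 6.5%, with 31 − 19 − 2 = 10 still pending. These counts meet dropout < 70% and, on the point estimate, retention > 70%. They fail dropout > 70%.

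**The case against.** **The criteria are soft.** Sections 4.1 and 5 present them as guidance and as a prompt for revisions. The Quantitative Analyses section commits separately to follow-up rates with 95% confidence intervals and to attrition proportions, so the true loss will be visible. This stands. A reader might infer that a binding go/no-go rule has been reversed and that the trial's decision will therefore be wrong, but the article does not describe a binding rule. Reporting the rates still does not say what rate was judged acceptable in advance, which is the purpose of the criterion.

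**No one would apply the absurd reading.** That is fair: no reader would demand more than 70% dropout. The lenient literal reading remains open, and the different sign placement gives it some support. It needs two conventions in one column and produces the idle ceiling shown in Step 4.

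**The intent is obvious.** Sections 2, 4.1 and 10 all speak of retention, which makes a retention threshold likely. It is still an inference, because the table does not say so and the source cited for the threshold is not available here. A reader might also infer that the sample size confirms it, since 0.70 × 80 = 56 lies within the "sample sizes of 50–60 being appropriate to assess the feasibility outcomes". Section 3.2 does not support that: it never says that 80 was inflated for attrition and never links it to Table 2.

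**The interim data make it moot.** They agree under the two plausible readings so far. The lower confidence limit is just below 70%, 10 participants were pending and 49 of the 80 were still to be recruited, so agreement at the end is not assured.

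**Conclusion.** The point holds as a mis-specified decision threshold. No input was miscalculated, so it is not an arithmetic error. As written, the attrition criterion either requires at least 57 of 80 dropouts or tolerates up to 55 of 80. Under neither convention, as go or stop criteria, does it agree with the adherence, helpfulness and negative-consequences rows. The likely intended criterion, more than 70% retained, allows at most 23 dropouts, so the literal reading is looser by 55 − 23 = 32 participants.

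The counts rest on the planned 80 being reached, on about 40 per arm for Step 4, and on the table's strict inequalities. That retention was meant is probable and needs the authors' confirmation. The documents do not show that the trial is failing on attrition: the interim point estimate meets the likely criterion comfortably.

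**What to change.** Before the remaining data are seen:

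1. Have the authors confirm whether the 70% was meant for retention.
2. If so, relabel the attrition rows and write them in words: study retention at 10 weeks more than 70%, and intervention retention more than 70% (equivalently, dropout less than 30%).
3. Write the other rows in the same convention: adherence more than 70%, reported as helpful more than 70%, substantial negative consequences less than 30%. Keep the strict inequalities unless the authors choose otherwise and say so; at 80 participants that choice moves the retention limit by one person.
4. Use all randomised participants as the denominator for study retention, so that pending or lost participants cannot fall out of the rate.

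The cost is a wording correction to Table 2 with a dated note. Randomisation, data collection and the descriptive analyses do not change.
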